### Objectives {7}

(1) Outcome: a 10-session BPD-specific guideline-based treatment produces more reduction in specific borderline symptoms than non-specific treatment as usual (TAU). (2) Global change: a 10-session BPD-specific treatment presents pre-post change in socio-cognitive processing (SCP) and emotion processing (EP), which is not the case in the TAU. (3) Treatment response: SCP and EP change more in treatment responders, compared to non-responders (across conditions). (4) Mediation: the changes in these potential mechanisms of change will function as mediators of symptom decrease (between intake, discharge and follow up; the latter will be used to disentangle potential time confounds). Change is operationalized on behavioral and neurofunctional (by controlling for the corresponding behavioral/idiographic information) levels. For post-therapy EP, we expect greater emotional variability when dealing with individualized self-criticism, along with lesser self-contemptuousness, compared with pre-therapy. It is expected that post-therapy neuronal activations are lower in a EP network involving areas in the PFC, the striatum and the insula-basal ganglia [57, 58], when compared with pre-therapy. For post-therapy SCP, we expect lower CCRT pervasiveness, when compared with pre-therapy and we expect that post-therapy neurofunctional activations are lower in regions associated with the theory of mind (i.e., anterior cingulate, precuneus, inferior and middle frontal gyri and inferior parietal lobes) [69–71], compared with pre-therapy.

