### Trial design {8}

The present study is planned as a randomized controlled treatment trial, involving a guideline-based psychiatric treatment (general psychiatric management (GPM) [20]) for BPD, over the course of a program comprising 4 months of treatment plus 12 months of follow up, in comparison with 4 months of TAU, by focusing on the underlying mechanisms of change. The outcome part is a superiority trial, while the mechanisms part focuses on controlled comparison of processes of change.

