### Outcomes {12}

The main outcome measure is the Zanarini Rating Scale for Borderline Personality Disorder (ZAN-BPD) [76]. The ZAN-BPD is a continuous hetero-administered measure assessing the nine criteria outlined in DSM-5, on a continuous Likert-type scale ranging from 0 to 4. As such, it yields a total theoretical score of 36. A comprehensive validation study has shown its reliability, validity and sensitivity to change [76].

Emotion processing related to self-criticism will be assessed using the self-criticism task. This task involves two main steps: (1) conduct of a two-chair dialogue on self-criticism, an individualized and therefore particularly emotion-arousing procedure [35, 54, 77] and observer’s process rating of the patient’s emotions using the Classification of Affective Meaning States (CAMS) [78] (see also [34, 47]) with the aim of extracting 20 individualized self-critical words for each patient at each assessment point. Increase in emotion flexibility (i.e., more different emotion categories as a reaction to the self-criticism) over time, along with a decrease in self-contemptuousness associated with the self-criticism over time, are indicators of productive change; (2) 1 week later, a test of neural correlates of the processing related to the 20 individualized self-critical words (extracted from step 1), in comparison with a set of 20 negative emotional [79], 20 positive emotional [79]), 20 neutral words and 20 non-words (symbols; in total 100 words; presented in a random order). Self-reported emotional arousal (on a self-assessment manikin (SAM)) and self-esteem (on the State Self-Esteem Scale (SSES)), along with observer-reported fear/shame (on the CAMS) reaction, will be measured as manipulation checks for step 1; SAM assessment will be performed for each stimulus presented in the scanner. This task was empirically tested in a non-published pilot study: in 5 individuals, we showed higher subjective arousal levels for the individualized words than for the standardized negative words, along with comparable neurofunctional activations.

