For the fMRI assessments, we will use the methodology of blood-oxygen-level-dependent (BOLD) imaging followed by standard data processing and statistical analysis in the framework of Statistical Parametric Mapping software (SPM12). The fMRI data will be acquired on a Siemens Prisma 3 T (64-channel head coil using a 2D echo planar (EPI) sequence). The acquisition parameters will be as follows: 3 × 3 × 3 mm3: echo time (TE) =30 ms, slice repetition time (TR) = 66 ms, 30 slices, flip angle = 90°. The structural MRI data consist of T1-weighted MPRAGE images (TR = 2000 ms; inversion time (TI) = 920 ms; α = 9°; bandwidth (BW) = 250 Hz/pixel; readout in inferior-superior direction; field of view (FoV) = 256 × 232 mm; 176 slices) at 1 mm resolution. All data pre-processing will be performed using the SPM12 (Wellcome Trust Centre for Neuroimaging, shttp://www.fil.ion.ucl.ac.uk/spm/) running under Matlab 7.13 (The MathWorks, Inc., Natick, MA, USA). EPI images will be realigned to the subject’s average image across trials (corrected for spatial distortions using the SPM fieldmap tools). The parameters of registration to standardized Montreal Neurological Institute (MNI)-defined space will be calculated on the anatomical image and the default settings of the “unified segmentation” framework followed by the diffeomorphic registration algorithm DARTEL [106, 107]. The spatial registration parameters will be applied to the functional time-series co-registered to the corresponding individual’s anatomical scan. Prior to statistical analysis, we will apply spatial smoothing with a Gaussian kernel of 8 mm full-width-at-half-maximum. All statistical analyses will be performed using the default settings in SPM12. The statistical analysis at subject-specific level will be performed using the general linear model (GLM) after convolving the event onsets with a canonical hemodynamic response function [108]. Both time points will be modeled as two separate sessions within the design matrices. For the EP task, at the subject level we will calculate the interaction between words (self-critical versus standard negative words; the non-words and the negative words will be excluded from the analyses, but used as control variables to ensure cognitive appropriateness) and time (time point 1 versus time point 2) using symbols as baseline. For the SCP task, the subject-level differential *t* contrast will test the interaction between ToM, PUN and time point (the control stimuli will be excluded from the data analysis, but will serve as control for cognitive appropriateness). For both tasks, we will use the one-sample *t* test with the outcomes and arousal changes associated with treatment as regressors for the group-level analyses. The differential contrasts at the group level will test for positive and negative correlation between the interaction at the subject-specific level and BOLD signal changes. Where appropriate, we will control for the corresponding behavioral data from the same assessment point.

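### The stated group-level fMRI model has no treatment-arm term, so it cannot test the neurofunctional part of hypothesis 2 (GPM versus TAU)

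*Protocol article*

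**What the plan says.** All references are to the protocol article.

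- **Objectives {7}.** Hypothesis 2 states that the 10-session treatment "presents pre-post change in socio-cognitive processing (SCP) and emotion processing (EP), which is not the case in the TAU". The same section adds: "Change is operationalized on behavioral and neurofunctional (by controlling for the corresponding behavioral/idiographic information) levels". Hypothesis 3 compares responders with non-responders across both conditions.
- **Trial design {8}.** The outcome part is a superiority trial, while "the mechanisms part focuses on controlled comparison of processes of change".
- **Outcomes {12}.** The two-chair dialogue for the EP task serves the aim of "extracting 20 individualized self-critical words for each patient at each assessment point". The SCP fMRI task uses set groups of cartoons.
- **Statistical methods {20a}, fMRI paragraph.** For EP, "at the subject level we will calculate the interaction between words" (self-critical against standard negative) and time. For SCP, the contrast is the interaction of theory-of-mind cartoons, visual puns and time. At group level, both tasks use the one-sample "test with the outcomes and arousal changes associated with treatment as regressors for the group-level analyses". The group-level contrasts "will test for positive and negative correlation between the interaction at the subject-specific level and BOLD signal changes".
- **Statistical methods {20a}, opening paragraphs.** Multilevel modeling is assigned to hypotheses 2 and 3 where appropriate, in text that opens with the behavioral assessments and all outcomes. HLM7 and SPSS23 are named for the behavioral indexes. Neural change appears there as a control variable, or combined with a behavioral change score in a composite.

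**The concern.** The neurofunctional claim in hypothesis 2 is a claim about two randomized arms. The fMRI paragraph is specific about the model at both levels, yet arm enters at neither. If that paragraph is followed, the trial produces no estimate of how neural change differs between GPM and TAU, and randomization plays no part in the fMRI results. A neural pre-post change could then be described but not credited to GPM, and a real difference between the arms could go untested.

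**Working it through.** **Inputs.** The models and hypotheses are those above. The effect size d = 0.60, two-sided alpha of 0.05, 30% dropout and N = 80 come from Sample size {14}. Equal allocation is assumed, as the ratio is not stated. The number of patients scanned is not given in the text, so 10, 15, 20 and 28 per arm are assumed. The top value is 80 × 0.70 / 2 = 28, which would need every patient remaining after the planned dropout to be scanned. The stated power of 0.819 is not tied to the scanned sub-sample, and this point does not depend on it.

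**Step 1: what the stated model estimates.** Let y be a patient's stimulus-by-time contrast, O the outcome change and A the arousal change. The stated model is

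y = b0 + b1·O + b2·A + error.

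With centered regressors and equal arms, b0 estimates (μ_GPM + μ_TAU)/2. The slopes b1 and b2 estimate association with outcome and arousal. Hypothesis 2 concerns μ_GPM − μ_TAU, and no coefficient equals that. The arousal regressor is a change score, not an arm indicator.

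**Step 2: the pooled mean does not track the arm difference.** Three cases, in SD units of y:

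| μ_GPM, μ_TAU | Pooled mean | Arm difference |
|---|---|---|
| 0.6, 0.6 | 0.6 | 0 |
| 0.6, 0 | 0.3 | 0.6 |
| 0.3, −0.3 | 0 | 0.6 |

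Share of 20,000 simulated trials significant at 0.05, given as one-sample test of the pooled mean / two-sample arm test:

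| Per arm | 0.6, 0.6 | 0.6, 0 | 0.3, −0.3 |
|---|---|---|---|
| 10 | 0.72 / 0.05 | 0.22 / 0.25 | 0.04 / 0.25 |
| 15 | 0.89 / 0.05 | 0.33 / 0.35 | 0.04 / 0.35 |
| 20 | 0.96 / 0.05 | 0.42 / 0.45 | 0.04 / 0.46 |
| 28 | 0.99 / 0.05 | 0.57 / 0.60 | 0.04 / 0.60 |

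The pooled mean is significant most often when hypothesis 2 is false (first case), and it misses an arm difference of 0.6 SD when the changes are opposite (third case). These columns describe the intercept only. They are not the error rate of the slope contrasts that the plan names.

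**Step 3: one-sample tests within each arm would not repair this.** The article does not propose them. If the true change is equal in both arms (0.6 SD), the chance of a significant result in GPM and not in TAU is p(1 − p), where p is the one-sample power in one arm:

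- 10 per arm: 0.396 × 0.604 = 0.24
- 15 per arm: 0.580 × 0.420 = 0.24
- 20 per arm: 0.721 × 0.279 = 0.20
- 28 per arm: 0.864 × 0.136 = 0.12

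**Step 4: power of the missing test.** For a two-sample t test the noncentrality is d·√(n/2):

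- n = 10: 0.6 × √5 = 1.34, power 0.25
- n = 15: 0.6 × √7.5 = 1.64, power 0.36
- n = 20: 0.6 × √10 = 1.90, power 0.46
- n = 28: 0.6 × √14 = 2.24, power 0.60

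**The case against.** Several counter-arguments have weight.

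**Another route exists.** The opening of Statistical methods {20a} gives multilevel models for hypotheses 2 and 3, and its composites contain change in neuronal regions of interest. A composite could therefore enter a model with arm. This stands only in part: a composite mixes behavioral and neural change, so an arm effect on it need not be neural.

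**The unseen analysis plan may add the contrast.** It may. But the article does not leave the group-level model open. It names one, and that model does not answer a hypothesis the same article states.

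**The pooled model has a proper use.** This stands. Hypothesis 3 runs across conditions, and a regression on outcome suits it. The model is incomplete for hypothesis 2, not wrong in itself.

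**A reader might infer more than the text supports.**

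- One might conclude that the plan would declare a shared time drift to be a treatment effect. For example, a drift of 0.5 SD in both arms with 28 scans in total makes the one-sample intercept significant with probability 0.72. The named contrasts, however, are slopes. A common drift does not inflate them; in simulation with an unrelated regressor they rejected 4.9% of the time.
- One might say that only the arm difference removes scanner drift or habituation. Drift common to both stimulus types is already subtracted within the patient.
- The problem of newly drawn stimuli belongs to the EP task and does not extend to the cartoons of the SCP task.
- The phrase "will test for positive and negative correlation between the interaction at the subject-specific level and BOLD signal changes" looks circular, since the interaction is itself a BOLD change. The preceding sentence names outcome and arousal change as regressors, so this is a wording slip.

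**Conclusion.** The point holds in this form: the only group-level fMRI model stated has no arm term, so it does not estimate GPM minus TAU. It cannot test the neurofunctional part of hypothesis 2 or deliver the controlled comparison promised under Trial design {8}. This follows from the form of the model and needs no sample-size assumption. Any pooled mean change could not be attributed to GPM, particularly in the EP task, where change in the words is mixed with change in the response to them.

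The power range of about 0.25 to 0.60 rests on assumptions: d = 0.60 applied to the fMRI contrast, 10 to 28 scanned per arm, equal allocation, and one test at 0.05 without correction for several regions.

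Severity is moderate. Hypothesis 1, the ZAN-BPD outcome and the behavioral part of hypothesis 2 are untouched, and the documents do not support a claim that the fMRI analysis as a whole is invalid.

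**What to change.** 1. **Add the arm test.** Name a GPM-versus-TAU comparison of the subject-level stimulus-by-time contrast (two-sample test or ANCOVA) in the EP and theory-of-mind regions as the test of the neurofunctional part of hypothesis 2.
2. **Keep the regression.** Retain the model on outcome and arousal change for the association questions in hypotheses 3 and 4, with arm added as a covariate.
3. **Correct the contrast sentence.** State that it tests the correlation of the subject-level interaction with outcome change and with arousal change.
4. **State the sub-sample size and power.** Give the expected number scanned per arm and the resulting power, so that a null arm result is not read as evidence of no difference.

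The cost is one extra SPM design and some wording; no new data are needed. Trial status describes the study as ongoing, so the contrast can still be fixed before analysis. The real price is low power for the arm test, which calls for cautious reporting and not for testing a different quantity.

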
### Interim analyses {21b}

No formal stopping rule of the trial is necessary, as the time limit of the recruitment phase (due to funding) will determine when the recruitment is stopped. In addition, we do not anticipate any specific problems that are detrimental to the participants.

### Methods for additional analyses (e.g., sub-group analyses) {20b}

No additional sub-group analyses will be performed.

#### Methods in analysis to handle protocol non-adherence and any statistical methods to handle missing data {20c}

Treatments with low adherence scores will still be included in the trial, but the level of adherence on the named scale will be included as a controlled variable on the level of the statistical analyses. For missing values, we will use classical methods of multiple imputations.

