### Intervention description {11a}

Brief treatment encompasses the communication about diagnoses, problem areas, anamnesis, the work on treatment focus, objectives and motivation, the treatment of treatment-interfering problems and the elaboration of interpretations related to the core concept of interpersonal hypersensitivity, according to the principles of GPM for BPD [20, 73–75]. For the TAU, 10 therapists will intervene using non-specific crisis management as usual (minimal ethical assessment and contact with the patient according to the local directives, ensuring safety management).

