### Strategies to improve adherence to interventions {11c}

Therapist adherence to the protocol will be self-assessed by the therapist using Gunderson’s (2016) questionnaire for adherence to GPM principles, to be filled in after each treatment.

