## Assignment of interventions: blinding

### Who will be blinded {17a}

The assessors (of outcome and mechanisms) and data analysts will be blind to the experimental condition, but the patients and the therapist will not. In order to control for bias, assessors will be polled at the end of the study with regard to each patient’s condition.

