## Statistical methods

### Statistical methods for primary and secondary outcomes{20a}

For the behavioral assessments and all outcomes, we will conduct intent-to-treat and completer analyses for all variables (hypothesis 1: outcome, defined as residual gains at discharge). We will use multilevel modeling [103] where appropriate, for hypotheses 2 and 3 (global change and treatment response). For hypothesis 4 (mediation), we will conduct a mediation analysis for both potential mechanisms of change [104]. Raw and composite scores for outcome and all mechanisms of change indexes will be used, by controlling for the corresponding fMRI data from the same assessment point. Composite scores for EP involve combining pre-post change in contemptuousness with change in neuronal regions of interest for individualized self-criticism. For SCP, this involves combining pre-post change in CCRT pervasiveness with change in neuronal regions of interest for theory of mind.

We will control for therapist effects in the three-level hierarchical linear modeling (HLM) [105]. All indexes (i.e., behavioral and fMRI) in the patient groups (*N* = 80) at intake will be rigorously compared with the indexes found in the healthy control group (*N* = 20); we expect systematic between-group differences, in the context of a control analysis. Statistical treatment packages HLM7 and SPSS23 will be used for the analyses of the behavioral indexes.

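### The GPM-adherence score is planned as a control variable without limit to one arm or a secondary analysis, so the adjusted arm coefficient would not estimate the randomised GPM-versus-TAU effect

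*Protocol article*

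**What the plan says.** Section {20c} keeps treatments with low adherence in the trial and then states that "the level of adherence on the named scale will be included as a controlled variable on the level of the statistical analyses". It does not restrict this to one arm, one hypothesis or a sensitivity analysis.

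The scale is identified in {11c}: "Therapist adherence to the protocol will be self-assessed by the therapist", on a "questionnaire for adherence to GPM principles, to be filled in after each treatment". Section {17a} says assessors and analysts are blind, "but the patients and the therapist will not".

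The comparator in {11a} has different content: "10 therapists will intervene using non-specific crisis management as usual". The article does not say whether TAU treatments are scored on the GPM scale. On incomplete data, {20c} says only: "For missing values, we will use classical methods of multiple imputations".

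The analyses concerned are in {20a}: "we will conduct intent-to-treat and completer analyses for all variables (hypothesis 1: outcome, defined as residual gains at discharge"), with multilevel models where appropriate for hypotheses 2 and 3. Section {8} gives the aim of the arm comparison: "The outcome part is a superiority trial".

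**The concern.** An intent-to-treat comparison estimates the effect of being allocated to GPM rather than TAU. A covariate measured before randomisation leaves that target intact. A covariate that the allocation itself influences does not, and adherence to GPM principles is such a covariate, because allocation decides whether the patient is offered GPM.

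There are two cases if the rule is applied to the arm comparison as written:

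- **TAU is scored.** Scores are likely to be lower than in GPM because TAU is not meant to deliver GPM. The arm coefficient then compares GPM and TAU patients at the same level of GPM adherence, which is not the randomised contrast.
- **TAU is not scored.** The covariate is undefined in one arm. It can enter only by imputation, with no observed TAU scores to support it, or by an arbitrary code.

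In both cases the coefficient tested under hypothesis 1, and the arm comparison in hypothesis 2, answers a different question from the superiority question in {8}.

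**Working it through.** **Inputs from the article.** 80 patients, d = 0.60, two-tailed alpha 0.05 and 30% dropout (section {14}).

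**Assumptions.** Allocation is 1:1, so 40 per arm; the article gives blocks of 10 but no ratio. The true effect on outcome is d = 0.60; {14} ties that figure to two concomitant mechanisms, not expressly to the main outcome. D is the distance between the arms on the adherence scale in within-arm SDs. b is the within-arm slope of outcome on adherence in SD per SD, positive when higher adherence goes with better outcome. The article gives neither D nor b, so ranges are shown.

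**Baseline power.** Section {14} states 0.819. A two-sided two-sample t test at d = 0.60 gives 0.755 with 40 per arm, and 0.597 with 28 per arm (80 × 0.7 = 56). The 0.819 is not reproduced on these inputs, and the test behind it is not named. Nothing below rests on it; 0.755 is the reference.

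**Precision.** With equal arms, the between-arm variance of the covariate is D²/4 and the within-arm variance is 1. The squared correlation with arm is therefore (D²/4)/(1 + D²/4), and the variance of the arm coefficient is multiplied by 1/(1 − r²) = 1 + D²/4. The unadjusted standard error is √(2/40) = 0.2236. At D = 2 it becomes 0.2236 × √2 = 0.316, and 0.60/0.316 = 1.90 gives power 0.47. At D = 3 it becomes 0.2236 × √3.25 = 0.403, and 0.60/0.403 = 1.49 gives power 0.31.

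**Bias.** The adjusted arm effect is 0.60 − b × D.

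| D | Variance factor | SE factor | Power, b = 0 | Estimate, b = 0.1 | Estimate, b = 0.2 | Estimate, b = −0.1 |
|---|---|---|---|---|---|---|
| 1 | 1.25 | 1.12 | 0.66 | 0.50 | 0.40 | 0.70 |
| 2 | 2.00 | 1.41 | 0.47 | 0.40 | 0.20 | 0.80 |
| 3 | 3.25 | 1.80 | 0.31 | 0.30 | 0.00 | 0.90 |

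Simulation (1,500 runs per scenario, 40 per arm) agrees. The adjusted estimates were 0.49, 0.41 and 0.31 for b = 0.1, and 0.39, 0.19 and 0.01 for b = 0.2. Power at b = 0 was 0.64, 0.47 and 0.28; a separate run of 4,000 at D = 3 gave 0.31.

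**Shared cause, no true effect.** Suppose adherence does nothing, but an unmeasured patient factor correlates 0.5 with adherence and carries a coefficient of 0.4 on outcome. The induced slope is 0.5 × 0.4 = 0.2. In 3,000 runs with a true null, the adjusted test rejected in 11%, 23% and 31% of trials at D = 1, 2 and 3; the unadjusted test stayed at 4% to 5%. The adjusted estimates averaged −0.20, −0.40 and −0.59, so these false rejections run against GPM. With the sign of the shared factor reversed they would favour GPM.

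**TAU unscored and coded 0.** If the GPM mean is m and its SD is s, the variance factor is (2 + m²/s²)/2. For m/s = 3 this is (2 + 9)/2 = 5.5, and power is about 0.21 with 40 per arm even without bias.

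**The case against.** The strongest reply is that {20c} does not list the models that receive the covariate, and {20a}, which sets out hypothesis 1, names no adherence term. A low GPM score counts as non-adherence only in a GPM treatment, so the authors may have meant a within-GPM analysis. Used that way, or centred within arm, the score would leave the arm comparison largely intact. Exact model terms are also something an article may leave to a fuller document.

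This stands as a plausible account of intent. It does not remove the point: {20c} states a rule, in general terms, and the restriction that would make it harmless is absent.

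It is also fair that {20c} keeps every treatment in, so the intent-to-treat population is preserved. What changes is what the adjusted coefficient estimates.

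A reader might go further and infer any of the following. The documents support none of them:

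- **The bias runs mainly toward no effect, so a real benefit would vanish.** That needs a positive slope and a large separation. With no slope and no shared cause there is no bias, and a negative slope exaggerates the effect.
- **The score is nearly the arm indicator.** This is an inference from what the scale measures; no TAU scores or arm separation are reported.
- **A whole arm will be imputed.** The article does not say that TAU is unscored, nor that imputation would cover the score.
- **Therapists rate adherence knowing the patient's outcome.** They are unblinded and rate after treatment, but the main outcome is rated by blinded assessors, and nothing says therapists see those ratings.

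**Conclusion.** The point holds in this form: as written, {20c} allows a post-randomisation score tied to the content of one arm into the superiority comparison, and the adjusted coefficient in hypotheses 1 and 2 would not be the randomised effect. That follows from what the scale measures and when, and needs no assumed figure.

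The size does rest on assumptions: 1:1 allocation, 40 per arm with no dropout, true d = 0.60, D between 1 and 3, and b of 0.1 or 0.2 in either direction. Over that range the harm runs from a modest loss of precision (variance factor 1.25, no bias) to an estimate of about 0.00, and a negative slope inflates the estimate instead. A shared unmeasured cause can also raise the error rate under a true null above 5%. The figures show what could happen, not what will.

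**What to change.** Replace the adherence rule in {20c} with a statement that:

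- adherence is left out of every model that compares the arms;
- adherence scores are reported descriptively, for TAU as well if it is scored;
- any analysis relating adherence to outcome is confined to the GPM arm and labelled exploratory.

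Keeping low-adherence treatments in the analysis should stay as it is. If a within-GPM analysis was always intended, this wording only makes it explicit.

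The cost is a sentence or so of text. No patients, assessments or new data are needed, and neither the sample size nor alpha changes.
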